### Adverse event reporting and harms

Physical activity may be a source of concern in the elderly. Adverse events may occur also during leisure activities, e.g., a fall during access to the room where the educational and leisure activities are held. During the trial, and thereafter during the follow-up, adverse events will be continuously collected and assessed at each visit. Adverse events monitoring will be recorded on an ad hoc schedule. Each adverse event will be reported including details about the type of adverse event, its beginning and end (date and time), its severity (from mild to severe), whether or not it could have been expected, its outcome (from completely solved to fatal), and whether or not it was related to the study (certainly/probably/possibly/unlikely/cannot say). Expected adverse events are those that can occur according to the activity (physical or leisure activity), such as muscle strain or fall. Unexpected adverse events are the sudden worsening of a pre-existing minor somatic disorder or cardiovascular events, such as stroke or heart attack, unrelated to the activity.

In case of serious adverse events, a written report will be prepared as per the ethical approval, with details about the participant and the nature of the event. Both the Regional Committee for Medical and Health Research Ethics, region of Sardinia, and the participant’s general practitioner will be notified about any serious adverse event, whether or not it was judged related to the study trial.

Participants incurring serious adverse events from moderate (requiring a relevant change in the treatment) to severe (requiring hospitalization) will be suspended from the study. Mild adverse events (requiring minimal change in the treatment or none at all, or some days of rest at home) will be not a reason for the termination of the trial. Data concerning participants that were suspended from the trial because of adverse events will be entered in the analysis by treatment allocated, as per the CONSORT statement [25].

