### Interventions

#### A. Physical exercise

The active intervention will consist in 3 sessions per week. PA was established as 60–84% of the Heart Rate Reserve (HRR); it will monitored continuously during activity and transmitted to the fitness professionals by a telemetry system. The individual HRR for each participant will be assessed according to the Estimated Maximal Heart Rate Formula. Baseline HR will be registered for all participants as a 3-day mean. PA consists of three phases: (1) *warm up,* 10-min, 60% of HRR; (2) *active phase*, 45-min, 60–84% HRR; (3) *cool down*, 10-min, < 60% HRR. The active phase was designed as a mixture of aerobic and anaerobic exercises, integrating drills of “life movements,” strength, and balance.

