### Oversight and monitoring

The coordinating center staff includes psychiatrists, psychologists, occupational therapists, and nurses, who will be responsible for patient enrollment and the assessment of psychosocial and exercise outcomes; anesthesiologist, cardiologists, internists, dermatologists, orthopedic surgeons, physiatrists, sport medicine physicians, who will be in charge of patient safety and clinical outcome assessment; and geneticists, biologists, laboratory staff, researchers, and data analysts responsible for storing and measuring biomarkers, collecting data, and compiling the case report forms and the database. The coordinating center staff will interlace with the activity of the researchers from the participating center.

The study will have a Steering Committee, a Data Safety Monitoring Committee, and a Quality Control Committee. The Steering Committee comprises the principal investigator, a forensic physician, a dermatologist, an engineer with expertise in gait analysis, an anesthesiologist, a statistician, and a psychiatrist, who also serves as data analyst. The Steering Committee oversees the advancement of the study, identifies problems and difficulties, and implements appropriate corrective measures. The Data Safety Monitoring Committee includes the principal investigator, a nurse, an occupational therapist, an anesthesiologist, and a cardiologist. It is in charge of study monitoring until the end of the follow-up with respect to the study implementation and progress and of making recommendations concerning the continuation, modification, or termination of the trial in relation to unforeseen adverse events of concern. The Quality Control Committee includes the principal investigator, a psychologist, a biologist, and a geneticist and will monitor the study for efficacy and safety. The Data Safety Monitoring Committee and the Quality Control Committee are completely independent from the sponsor that funded the study.

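### The definition of unexpected adverse events has causality built into it, so an exercise-related stroke or heart attack cannot be recorded as both unexpected and related

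*Protocol article*

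**What the plan says.** All the event definitions are in the protocol article, section *Adverse event reporting and harms*.

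- Each event is described by several items. One is expectedness: "whether or not it could have been expected". Another, listed separately, is causality: "whether or not it was related to the study (certainly/probably/possibly/unlikely/cannot say".
- Expected events are defined thus: "Expected adverse events are those that can occur according to the activity (physical or leisure activity), such as muscle strain or fall".
- Unexpected events are the sudden worsening of an existing minor somatic disorder, or "cardiovascular events, such as stroke or heart attack, unrelated to the activity".
- Collection has no filter: "adverse events will be continuously collected and assessed at each visit". For serious events, the ethics committee and the participant's general practitioner "will be notified about any serious adverse event, whether or not it was judged related to the study trial".

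Two other sections bear on the point. Under *A. Physical exercise*, the active phase is set at "45-min, 60–84% HRR", in the exercise arm only. Under *Oversight and monitoring*, the Data Safety Monitoring Committee makes recommendations on continuing the trial, or on its "modification, or termination of the trial in relation to unforeseen adverse events of concern".

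**The concern.** Expectedness and causality answer different questions. Expectedness asks whether this kind of event was foreseen for this intervention. Causality asks whether the intervention brought about this particular event. Safety review needs both, because an event that was not foreseen and is judged related is the usual reason to look at a trial again.

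The section names the two items separately and then makes one depend on the other. The event most affected is a cardiovascular event during or after exercise, and only one arm exercises. The *Discussion* names finding out which adverse events occur in elderly people doing physical activity as an aim of the study. *Power analysis and statistical analysis* plans no interim safety analysis, so in-trial safety judgement rests on how individual events are described and passed to the committees.

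**Working it through.** The article gives no adverse-event rate and no safety threshold, so there is no figure to reproduce. The check is to set the definitions side by side and follow one event through them.

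**Step 1. The classification the form implies.** Expectedness has 2 levels and relatedness has 5, which gives 2 × 5 = 10 combinations. Three of these describe an event that is unexpected and at least possibly related: unexpected with certainly, with probably, and with possibly.

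**Step 2. A heart attack judged probably related to the active exercise phase.** The phrase about being unrelated to the activity can be read in two ways.

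| Reading of the phrase | Expectedness label | Consequence |
|---|---|---|
| Descriptive: cardiovascular events are, as a kind, unrelated to the activity | Unexpected | The label presumes the event is unrelated, which contradicts a grade of probably related on the causality item |
| Restrictive: only those cardiovascular events that are in fact unrelated are meant | Not unexpected; it can fall only among events the activity may bring about, so expected | The event is labelled as foreseen, alongside muscle strain and falls |

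On the first reading, the three combinations in Step 1 contradict the definition for cardiovascular events. On the second, the definition excludes them. Neither reading allows a coherent record of unexpected and activity-related.

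**Step 3. Fit with the causality scale.** The five levels are certainly, probably, possibly, unlikely and cannot say. None of them is unrelated. The definition of unexpected therefore relies on a judgement that the assessor has no box to record.

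**Step 4. Fit with the committee's remit.** The Data Safety Monitoring Committee's recommendations are tied to unforeseen events, with no condition on relatedness.

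- On the descriptive reading, a heart attack is labelled unexpected and comes within the remit.
- On the restrictive reading, a related heart attack is labelled expected. If unforeseen is taken to mean not expected, a related event falls outside the wording while an unrelated one falls inside it. That is the wrong way round for a safety body.

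**Step 5. What does not depend on the label.** Collection is continuous. Notification of serious events ignores relatedness. Suspension from the study follows severity. The relatedness grade is a separate entry, and no rule derives it from the expectedness label.

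**The case against.** The strongest reply is that this is loose drafting without a consequence. Relatedness is graded for every event, so an exercise-triggered heart attack can be recorded as certainly, probably or possibly related. The expected class is open, since strain and falls are only examples, so on the restrictive reading a related cardiovascular event does have a place. No collection or notification step turns on the label. The layout of safety tables is commonly left to the full protocol, the event form or the analysis plan, none of which is shown.

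Most of this stands, and it rules out three stronger conclusions that a reader might draw:

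- *That such an event has no valid category, or must be coded unrelated.* The separate causality item accepts any of its five grades, and unrelated is not one of them.
- *That related cardiovascular events would be reported as none among the 60 participants planned for the exercise arm.* The relatedness field would show whatever grade was given. Only the combination of unexpected and activity-related is ruled out.
- *That safety is understated.* Events are collected without a filter and serious ones are notified regardless of relatedness. Nothing in the article says that harms will be counted only if unexpected or only if related.

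The reply does not rescue the definition. The restrictive reading avoids the contradiction only by labelling an exercise-related stroke or heart attack as expected. This is also not a detail left to another document: the article states the definition, and states it wrongly.

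**Conclusion.** The point holds as a wrongly stated operational definition of minor severity. For cardiovascular events, unexpected and activity-related cannot coherently be recorded on either reading of the text. The effect is confined to the expectedness label and to what leans on it.

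Two knock-on effects are possible but not demonstrated. First, a definition that presumes cardiovascular events are unrelated may pull an assessor towards a lower relatedness grade. *Ethical issues* accepts that asking participants what they were doing reveals their arm, so masking cannot be relied on to prevent this. Second, the committee's remit may miss a related event. That requires both the restrictive reading and the assumption that unforeseen means the same as unexpected.

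No numerical size can be given, because the documents state no event rate. Sample size, power, type I error and the efficacy analysis are untouched.

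**What to change.** In *Adverse event reporting and harms*:

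1. Delete the words about being unrelated to the activity from the definition of unexpected events.
2. Define expectedness without reference to causality, for example against a list of foreseen event types fixed for each condition.
3. Grade relatedness only on the existing five-level scale.
4. Report events by arm with expectedness and relatedness as independent items, so that unexpected and related events are visible.

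It would also help to state in *Oversight and monitoring* whether unforeseen means unexpected as defined in the adverse-event section.

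The cost is a reworded definition and a small change to the event form, with no extra visits or staff. *Trial status* gives June 2020 as the planned end of data collection, so in practice the work is mainly to re-read events already coded. The details required for each event should make that feasible. The re-reading should be done without changing relatedness grades unless the event record itself supports a change.

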We have pioneered the clinical trials and systematic reviews on this topic [3, 13]. The multidisciplinary project we propose is an opportunity to address the above-mentioned issues and to gain further knowledge in the field of active aging. In particular, this study aims at measuring—through a randomized controlled trial—whether an intervention based on moderate PA can improve quality of life (QoL) and motor skills of the elderly living in the community (primary outcomes). The secondary objectives are to measure whether physical activity improves (1) cognitive performance, (2) perception of pain, (3) biological rhythms and immune response linked to metabolic control, (4) community assets (settings, mobility safety, social cohesion), and (5) growth factors and neurotransmitters in the periphery similarly to outcomes in animal studies. The study will also allow investigating the correlation between psychological/motor improvement and the biological markers. The trial will be followed by a 48-week follow-up to investigate whether and to what extent can PA prevent disability and depressive disorders.

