## Methods

This is a 12-week randomized controlled trial (RCT) with subsequent 48-week (circa 12 months) follow-up.

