### Follow-up testing at 6 months

The 6-month (24 weeks) testing includes both a medical examination and the psychological testing as in the baseline (pre-treatment) period. However, no laboratory test will be conducted.

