### Primary outcomes

The primary outcomes are quality of life, walking speed, and postural sway. All primary outcomes will be aggregated according to their mean and the outcome will be assessed as a change from the baseline. Table 2 lists the main characteristics of the primary outcomes according to their elements as in Saldanha et al. [24].

**Table 2 Tab2:** Elements of the completely specified primary outcomes

Domain	Measurement	Metric	Aggregation	Time-point
Quality of life	SF-12	Change from baseline	Mean	At week 12 (end of treatment) At week 48 (end of follow-up)
Walking speed	Gait analysis	Change from baseline	Mean	At week 12 (end of treatment)
Postural sway area	Stabilometry	Change from baseline	Mean	At week 12 (end of treatment)

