### Methods to handle missing data

We do not expect many missing data since the study will be carried out within just one center and the interventional trial has a short duration (12 weeks). However, missing data may occur during the follow-up period. Thus, in the primary analysis, missing data will be replaced by “last-observation-carried-forward.” Then, multiple imputations will be used for sensitivity analyses.

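### Suspending participants from the study after a serious adverse event, with no provision for further testing, lets a pre-event SF-12 score stand as the week-48 primary result

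*Protocol article*

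**What the plan says.** Adverse event reporting and harms sets the rule: "Participants incurring serious adverse events from moderate (requiring a relevant change in the treatment) to severe (requiring hospitalization) will be suspended from the study". The sentences that follow say that mild events do not lead to termination, and that data from suspended participants enter the analysis by allocated treatment. The same section states: "During the trial, and thereafter during the follow-up, adverse events will be continuously collected and assessed at each visit".

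Two other sections have rules of the same form. Procedure and setting withdraws from the study anyone whose new treatment removes eligibility for non-competitive physical activity. Ethical issues discontinues from trial participation anyone whose health condition precludes going on. None of the three sections says whether the person is still tested.

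The design is described as follows: "This is a 12-week randomized controlled trial (RCT) with subsequent 48-week (circa 12 months) follow-up". No activity is given in follow-up, only testing: "The 6-month (24 weeks) testing includes both a medical examination and the psychological testing as in the baseline (pre-treatment) period". Table 2 makes SF-12 change from baseline a primary outcome at week 12 and again at week 48. The Background gives the purpose of the follow-up: "The trial will be followed by a 48-week follow-up to investigate whether and to what extent can PA prevent disability and depressive disorders".

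Power analysis and statistical analysis includes everyone with baseline data. Methods to handle missing data then states: "Thus, in the primary analysis, missing data will be replaced by" the last observation carried forward. It adds: "Then, multiple imputations will be used for sensitivity analyses".

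**The concern.** Analysis by allocated treatment keeps the person in the arm, but it also needs the outcome measured after the event. Here one rule can stop that measurement for the participants most likely to have worsened, and another replaces it with an earlier score. If the event falls between t1 and t3, week-48 quality of life may look maintained in someone who has since been admitted to hospital. That sits badly with a follow-up meant to show whether exercise prevents disability. The multiple-imputation sensitivity analysis does not repair this. With no post-event scores from suspended participants, it has to borrow from those who stayed.

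**Working it through.** **Which value is used at week 48, by time of event, if testing stops**

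| Event | Value carried to week 48 | Consequence |
|---|---|---|
| before t1 | t0 | change is 0: counted as not improved; a real decline enters a mean change as zero |
| between t1 and t2 | t1 | pre-event status stands |
| between t2 and t3 | t2 | pre-event status stands |

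In every row the value predates the event. An improved status can be preserved only in the last two rows, and those need suspension to apply in follow-up.

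**The plan's own effect size.** Power analysis and statistical analysis gives h = 0.45, a difference of 0.215 and NNT 5. With h = 2(arcsin√pE − arcsin√pC), two pairs of proportions fit both figures: pE 0.475 with pC 0.26 (pair A), and pE 0.74 with pC 0.525 (pair B). Each gives h = 0.45 and a difference of 0.215. 1/0.215 = 4.7, which rounds to the stated NNT of 5.

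**Assumptions.** The article gives no event rate, so the shares suspended after t1 (aE, aC) are assumed. Status at t1 persists in those who stay. Every suspended participant is truly not improved at week 48.

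**Formula.** The carry-forward difference is pE − pC = 21.5 points whatever the rates. The true difference is pE(1 − aE) − pC(1 − aC).

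| aE / aC | True difference, pair A | True difference, pair B | Error of carry-forward (points) |
|---|---|---|---|
| 5% / 5% | 0.215 × 0.95 = 0.204 | 0.204 | +1.1 |
| 10% / 10% | 0.215 × 0.90 = 0.1935 | 0.1935 | +2.2 |
| 15% / 5% | 0.475 × 0.85 − 0.26 × 0.95 = 0.157 | 0.74 × 0.85 − 0.525 × 0.95 = 0.130 | +5.8 / +8.5 |
| 5% / 15% | 0.475 × 0.95 − 0.26 × 0.85 = 0.230 | 0.74 × 0.95 − 0.525 × 0.85 = 0.257 | −1.5 / −4.2 |

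In the third row the true NNT is 1/0.157 = 6.4 or 1/0.130 = 7.7, against 4.7 shown. In the fourth it is 1/0.230 = 4.3 or 1/0.257 = 3.9.

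**Scale.** The standard error of the difference with 60 per arm is √[(0.475 × 0.525 + 0.26 × 0.74)/60] = 0.086, or 8.6 points. Pair B gives the same value.

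**The case against.** The strongest objection is to the reading. The article often uses the word trial for the 12-week period alone: the Background has the follow-up come after the trial, Treatment calls week 12 the end of the trial, and Methods to handle missing data gives the interventional trial a 12-week duration. The harms section restates the rule as suspension from the trial, and Table 1 draws adverse-event monitoring over the treatment column only. On that reading, suspension stops the sessions or applies only before t1, where carrying baseline forward gives no upward bias in the proportion improved. This stands as a real ambiguity. It does not remove the point, because the operative sentence says study, sets no time limit, and nothing provides for later testing.

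A second objection is that a condensed article may leave continued testing to the full protocol. It may. But the article itself states the suspension rule, the analysis set and the imputation rule, and the fault lies in how these combine.

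Third, a reader might infer that carry-forward necessarily flatters exercise. The documents do not support that. Neither arm receives activity after t1, no reason is given to expect more late events in the exercise arm, and the trial's own hypothesis that exercise prevents disability points to fewer. With the rates reversed, carry-forward understates the benefit. Equal rates cost only 1.1 to 2.2 points, small beside a standard error of 8.6. The assumption that all suspended participants are truly not improved is also severe, since a moderate event means only a relevant change in treatment.

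Finally, suspension after t1 leaves walking speed, postural sway and week-12 SF-12 untouched. Only one time point of one of the three primary outcomes is exposed to it.

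**Conclusion.** The point holds as a fault in stated rules: followed as written, they allow a pre-event SF-12 score to be analysed as the primary week-48 result. Its reach into follow-up is inferred from the collection of events there; no sentence says outright that suspension applies after t1. The direction of bias is not known. On the assumptions above, it runs from 8.5 points of overstatement to 4.2 points of understatement, depending on which arm has more late suspensions. The documents support neither a claim that the exercise effect will be inflated nor a claim that suspended participants are certainly left untested. The weakness is worth correcting because the remedy is cheap and leaves the safety trigger as it is.

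**What to change.** In Adverse event reporting and harms, Procedure and setting, and Ethical issues, limit suspension, withdrawal or discontinuation to the assigned activity. State that t1, t2 and t3 testing continues where the participant is able and willing. SF-12 is a self-report questionnaire and can be taken by phone or post.

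Data collection was planned to end in June 2020, so rewording may come too late. In that case, report by arm how many participants were suspended before and after t1 and how many were tested afterwards. Add a week-48 SF-12 sensitivity analysis that counts untested suspended participants as not improved.

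This should stay a sensitivity analysis. It is another single imputation. If it were made primary, power with 60 per arm (two-sided 0.05 score test, by enumeration) would fall from 69.3% to 62.6% (pair A) or 58.5% (pair B) at 10% suspended per arm.

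The cost is a few questionnaire contacts, or one table and one extra analysis. Nobody resumes exercise, so no safety risk is added.
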